### Blinding

Because men will know which arm of the study they are in, blinding is not possible. However, because randomisation occurs later, group allocation will not be known to either participants or field staff at baseline assessment. The primary outcomes for the trial will be measured by and downloaded directly from the activPAL, which gives an objective measurement of activity pattern that is not accessible to either research staff or participants until it has been processed. The researchers who process activPAL data will be blind to group allocation.

### Procedures

We will collect data at baseline, and at follow-up assessments immediately post-program and 12 months after baseline. At six months, participants will be asked to complete an additional short online questionnaire for the economic evaluation. Full details of the measures are provided below and the timing of each measurement is provided in Table 1.

**Table 1 Tab1:** Summary of measures used in the EuroFIT trial

	Baseline	Post-program	6 Months	12 Months
Objective physical activity and sedentary time				
activPAL^tm^ micro	X	X		X
activPAL wearing diary (sleep, work time)	X	X		X
Self-reported behaviours				
Food intake (adapted DINE)	X	X		X
Physical activity (IPAQ-short)	X	X		X
Domain specific and total sedentary time (Marshall)	X	X		X
Sleeping time	X	X		X
Standing time	X	X		X
Sedentary/active behaviours (Activity Choice Index)	X	X		X
Smoking	X	X		X
Objective physical measures				
Body height	X			
Body weight	X	X		X
Waist circumference	X	X		X
Resting blood pressure	X	X		X
Blood biomarkers	X			X
Self-reported health and psychosocial measures				
Wellbeing (Cantril ladder)	X	X		X
Self-esteem (Rosenberg)	X	X		X
Vitality	X	X		X
Quality of Life (EQ-5D-5 L)	X	X		X
Long standing illness, disability or infirmity	X	X		X
Joint pain	X	X		X
Injuries	X	X		X
Self-reported socio demographic moderators				
Age	X			
Ethnicity	X			
Marital status	X			
Education	X			
Current employment status	X			
Income	X			
Self-reported mediators				
Motivation for physical activity (adapted BREQ-2)	X	X		X
Ego/Task involvement	X			X
Club identification (Sport Spectator Identification Scale)	X	X		X
Weight management strategies	X	X		X
Weight loss activities	X	X		X
Self-reported mediators (intervention group only)				
Need support of coach		X		
Need thwarting by coach		X		
Mastery/performance climate		X		
Relatedness to group		X		
Need satisfaction from physical activity				X
Self-reported cost-effectiveness				
Health-related quality of life (EQ-5D-5 L)	X	X	X	X
Health care use (iMTA)		X	X	X
Consequences for employment (iPCQ)		X	X	X
Medication use (iMCQ)	X			X
Travel costs to club	X	X		X
Self-reported process evaluation (intervention group only)				
Coaches	X	X		
Participants	X	X		X

Measurement sessions will be held at the football clubs during evenings, in order to maximise attendance of participants. All measurements will be conducted by researchers/fieldworkers trained by study staff to standardised protocols. Men who opt into the blood testing will have a venous blood sample taken using trained nurses/bioengineers. Participants will be asked to complete a questionnaire (either paper-based or on a tablet provided by the research team). Sufficient staffing will be provided at measurement sessions to allow assistance to be available for men with low literacy or other difficulties in completing the questionnaire. In line with best practice, country validated versions of the questionnaire will be used when available. For parts of the questionnaires lacking official validation, translation will be done by members of the EuroFIT research teams and back-translated into English by the principal investigators in each country.

#### Fieldwork staff training

Fieldwork staff training will be standardized and quality assured. We will organise a training meeting for research leads from each country who will then train the fieldworkers locally. Standard operating procedures will describe all aspects of trial delivery including specification of equipment used in the measurement sessions and any adaptations to survey instruments that are necessary in different country/cultural settings.

#### Measurement feasibility study

The baseline and post-program measurement protocols have been tested during a feasibility study that was conducted between September 2014 and February 2015 in all four participating countries (1 club in the Netherlands, Norway and UK, and 2 clubs in Portugal). In total, 57 men participated in the feasibility study. Lessons learned were incorporated into the final study protocol.

#### Procedures to maximise retention to the trial

To maximise retention at the follow-up assessments we will:Send men an advance reminder that follow-up measurements are upcoming, using a personalised letter/e-mail sent 2–4 weeks ahead of the measurement dates at their club;Phone men two weeks before the scheduled post-program and 12 month measurement sessions to arrange an appointment time for the measurements;Send a confirmation of the date, time and location of the man’s appointment by e-mail/mail (according to men’s individual preferences);Text men in the days leading up to their appointment to remind them about the time, date and location;Offer men who do not show up at first measurement visit a second opportunity for measurement at the club;Offer men a home/university visit if they cannot attend or fail to attend the follow-up assessments at the club;Offer men who have successfully completed a follow-up assessment, a club voucher in appreciation of their time.

#### Primary outcomes: objective physical activity and sedentary time

The primary outcomes in this trial are changes in total physical activity (i.e. steps per day) and total sedentary time (i.e. minutes per day spent sitting). This will be objectively assessed with the activPAL activity monitor (model activPAL^TM^ micro; PAL Technologies Ltd., Glasgow, UK). The activPAL is a small monitor that weighs 9 g and is taped to the front of the thigh ideally for at least seven complete consecutive days. It has no display screen; hence the data recorded by the activPAL are not visible without being downloaded and processed. The activPAL has been found to have good measurement properties to assess sitting, standing, stepping and postural transitions in adults [30–32].

Once consent is obtained at the information meeting, trained researchers/fieldworkers will provide participants with face-to-face instruction on how to affix the activPAL to the thigh. The face-to-face instruction will be supported by written guidance on how to fit the activPAL. Participants will be asked to wear the device 24 h per day (including while taking a shower) for seven consecutive days; they will be advised that they should only temporarily remove the device during water submersion activities (e.g. having a bath, swimming) and to refit the device as soon as possible afterwards. Participants will be asked to keep a monitoring log to note any times when the device was removed and replaced. Participants will also be asked to record work and sleep times in the monitoring log. At baseline, the activPAL will be returned when the participant attends the baseline measurement session at the club. At both post-program and 12 month follow-up assessments, participants will receive the activPAL and written instructions by mail for fitting and wearing the device ten days before the follow-up measurement is scheduled at their club. Each participant will receive a reminder text message to remind them to wear the device. Mail delivery of the activPAL was successfully trialled in the feasibility study.

In order to meet the inclusion criteria for the trial, as described above, participants need to provide at least four valid days of activPAL data at baseline. Data from the attachment and removal day will not be used for analyses as these are incomplete days where the participant started or finished wearing the activPAL during the day. ActivPAL data will be considered valid when the participant wore the device for at least 10 h of the waking day.

#### Secondary outcomes

##### Self-reported behaviours

Using an adapted version of the Dietary Instrument for Nutrition Education (DINE) questionnaire [33], we will assess self-reported dietary behaviour via the frequency of intake of the following foods and drinks: cheese, burgers or sausages, beef, pork or lamb, fried food, chips or French fries, bacon or ham or pate, savoury pies, pasties, sausage rolls and pork pies, savoury snacks, consumption of fruit, vegetables (not potatoes), chocolate, sweets, biscuits, sugary drinks (fizzy drinks, diluting/ fruit juice) and milk. We will also assess frequency of breakfast consumption and alcohol consumption.

Self-reported physical activity will be recorded using the International Physical Activity Questionnaire (IPAQ), which assesses walking, other moderate intensity physical activity and vigorous intensity physical activity [34]. Self-reported sedentary time will be assessed with the Marshall questionnaire [35], which assesses total and domain specific sitting time (i.e. sitting during transport, at work, while watching TV, while using the computer for leisure, and during other leisure activities). We will assess both sleeping and standing time using a single item question (*How many hours in each 24 h day do you usually spend: Sleeping (including at night and naps);* or *Standing* [36]). We will capture activity and sedentary behaviours by using the Activity Choice Index [37], measured on a 5-point scale (from ‘never’ to ‘always’). Items include: using stairs instead of escalators or lifts; walking instead of driving or taking public transport; parking away from destination or getting off public transport early to have a longer walk; using work breaks to be physically active; choosing to stand up instead of sitting; choosing to do things by hand instead of using mechanical/automatic tools.

In addition, smoking behaviour will be assessed, including date of quitting and amount of current consumption, when relevant.

##### Objective physical measures

Body height will be measured (to the nearest 1 mm) using a portable stadiometer (Leicester Height Measure) at baseline only after participants have removed their shoes. Body weight will be assessed at all measurements (to the nearest 0.1 kg) using a calibrated electronic flat scale (Tanita HD366). Participants will be allowed to wear light clothes (such as shorts and t-shirts), but will be asked to remove any heavy items of clothing, their shoes and any items in their pockets. We will calculate BMI as weight in kilograms divided by the square of height in metres (kg/m^2^). Waist circumference will be measured twice (to the nearest 0.1 cm) with a Seca 201 measure, with participants asked to remove their shirts. If the difference between the two waist measures is more than 0.5 cm, a third measurement will be conducted. The mean will be calculated from the two nearest measures.

Resting blood pressure will be measured with an Omron 705-CPII blood pressure monitor after 5 min sitting still. If measured systolic blood pressure is over 139 mmHg and/or measured diastolic blood pressure is over 89 mmHg, two further measures will be taken and recorded, and in line with duty of care, men will be given letters advising them to consult their GP. A mean will be calculated from the second and third measures.

Blood samples will be taken at baseline and after 12 months from those who provide the additional consent for this measure. Participants who have opted-in to provide blood samples will be asked to confirm that they have fasted for at least 6 h. Time of last food/drink (other than water) intake will be recorded on the electronic Case Report Form (eCRF). A venous blood sample (using 1 × 9 ml Ethylenediamine Tetraacetic Acid (EDTA) tube, 1 × 7 ml Serum-separating tubes (SST), and 2 × 2 ml fluoride oxalate) will be taken by a trained phlebotomist (usually a fieldwork nurse) using a standard operating procedure. Samples will be stored at 4 °C (either in a refrigerator, cool bag with ice pack or on wet ice) until processing at a local hospital, laboratory, or onsite within 24 h (ideally within 12 h) (42). Two 1 ml aliquots of whole blood from the EDTA tube will be dispensed into barcoded screw-cap Eppendorf tubes. All blood tubes will then be centrifuged at 3000 rounds per minute for 20 min at 4 °C to separate red cells /plasma/serum. The SST will be allowed to clot for at least 30 min after collection before spinning. After spinning, 0.5 ml aliquots will be pipetted with plasma (5 from EDTA tube, 2 from fluoride oxalate tubes) and serum (5 from SST). These will be stored in barcoded tubes at −80 °C in barcoded boxes in an alarmed freezer, with capability to transfer samples promptly into a spare freezer in the event of freezer breakdown. Time of sample collection, start of sample processing and freezing will be recorded in the eCRF. At the end of baseline collection for each country (except for the UK where they will be delivered directly following baseline collection at each club), all baseline samples will be shipped to the Institute of Cardiovascular and Medical Sciences at the University of Glasgow in a single consignment by using World Courier (http://www.worldcourier.com), where they will again be stored at −80 °C. Similarly, the 12-month blood samples will be shipped to Glasgow in a single consignment after all these samples have been collected in each country (except for the UK, as described above).

All blood samples will be analysed at the end of the trial. If analysis of the blood data shows a high risk for any of the cardio-metabolic disease biomarkers that the participant should be aware of, we will inform the participant.

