This paper describes the protocol for a randomised controlled trial, which aims to evaluate the effectiveness and cost-effectiveness of the EuroFIT program in supporting men to improve their lifestyles versus a waiting list comparison group that is offered the program after the 12-month follow-up. The primary aim of the trial is to determine whether EuroFIT can help men aged 30–65 years with a self-reported Body Mass Index (BMI) ≥27 kg/m^2^ to increase their physical activity and decrease their sedentary time over 12 months. Secondary outcomes are weight, BMI, waist circumference, resting systolic and diastolic blood pressure, cardio-metabolic blood biomarkers (e.g. glucose, insulin, HbA1c, lipids and liver function), food intake, self-reported physical activity and sedentary time, wellbeing, self-esteem, vitality and quality of life. Cost-effectiveness will be assessed and a process evaluation conducted.

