#### Effectiveness analysis

In accordance with the study aims, statistical analyses will be conducted to determine whether the intervention group differs from the comparison group in changes over time in primary and secondary outcomes. The key analysis will be undertaken on an intention-to-treat basis, regardless of individual engagement with the EuroFIT program. However, further sensitivity analyses will determine the association between attendance at intervention sessions and effectiveness. Analysis of outcomes at each time point will use linear mixed effects regression methods (normal, logistic or other generalised linear models, as required), including random effects for country and football club, and fixed effects for study group and baseline measurement of the outcome. Regression models will be extended to assess moderators and mediators of intervention effects. The patterns and extent of missing data will be examined and, if necessary, methods such as multiple imputation will be implemented to provide robust results for primary and main secondary outcomes, assuming data are missing at random.

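### Blood pressure is a single reading at or below 139/89 mmHg but the mean of readings two and three above it, so this secondary outcome is defined by its own level, and a real effect would shrink if readings fall within a visit

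*Protocol article*

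**What the plan says.** The section Objective physical measures describes one reading for everyone: "Resting blood pressure will be measured with an Omron 705-CPII blood pressure monitor after 5 min sitting still". More readings depend on the level of that reading: "If measured systolic blood pressure is over 139 mmHg and/or measured diastolic blood pressure is over 89 mmHg, two further measures will be taken". The averaging step follows: "A mean will be calculated from the second and third measures". No repeat or average is given for men at or below the threshold.

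In the same section, waist circumference is measured twice in every man, and the extra measurement depends on disagreement between readings, not on level: "If the difference between the two waist measures is more than 0.5 cm, a third measurement will be conducted".

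Systolic and diastolic pressure are named secondary outcomes (Background). Table 1 schedules them at baseline, post-program and 12 months, so the rule operates at all three visits. The model under Effectiveness analysis has "fixed effects for study group and baseline measurement of the outcome", so pressure recorded under this rule enters both as outcome and as covariate.

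**The concern.** Which quantity is analysed depends on the first reading. A man just under the threshold keeps that reading, with its full measurement error and any first-reading excess. A man just over it is represented by two later readings, which on average lie lower through regression to the mean and, possibly, settling during the visit. The error variance is that of one reading on one side and half of it on the other.

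If the programme lowers pressure, fewer intervention men cross the threshold at follow-up, so the comparison arm receives more of the downward replacement. What is at stake is the size of the blood pressure effect in mmHg. A later analysis plan cannot restore the second and third readings in men below the threshold, because they are never taken.

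**Working it through.** The document gives no blood pressure SD, within-visit SD, order effect or expected effect, so there is no stated figure to reproduce. Every blood pressure input below is an assumption, shown over a range.

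**Rule.** Let R1, R2, R3 be the readings. The analysed value is Y = R1 if R1 is at or below 139/89, and Y = (R2 + R3)/2 otherwise.

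**Jump and precision at the threshold.** Assume mean systolic 130, between-man SD 14, within-visit SD 5 and a fall of 3 mmHg after the first reading. A man first read at 139 is analysed at 139. For a man first read at 140, triggered on systolic pressure, the expected later mean is 130 + [196/(196 + 25)] × 10 − 3 = 135.9 (138.9 with no fall). The error SD is 5 below the threshold and 5/√2 = 3.5 above it.

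**Effect on the between-arm difference.** Let d be the fall from reading 1 to readings 2 and 3, Δ the true effect, and p_C and p_I the shares re-measured in the comparison and intervention arms. The trigger uses R1 only, so these shares do not depend on d, and

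estimated/true(d) = estimated/true(0) − d × (p_C − p_I)/Δ.

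The first term carries regression to the mean alone. The second is the differential use of the lower readings.

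**Simulation.** 2,000,000 men per arm, rule applied literally; between-man SD 14, Δ = 3 mmHg systolic (1.8 diastolic), diastolic fall half the systolic one. Results for systolic pressure:

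| Mean SBP | Within-visit SD | Re-measured, comparison / intervention | Ratio, d = 0 | d = 3 | d = 6 |
|---|---|---|---|---|---|
| 130 | 5 | 32.3 % / 25.1 % | 0.984 | 0.913 | 0.841 |
| 130 | 8 | 35.5 % / 28.5 % | 0.970 | 0.900 | 0.829 |
| 135 | 5 | 45.7 % / 37.5 % | 0.993 | 0.912 | 0.829 |
| 135 | 8 | 48.3 % / 40.5 % | 0.991 | 0.913 | 0.835 |
| 140 | 5 | 59.6 % / 51.3 % | 1.005 | 0.922 | 0.837 |
| 140 | 8 | 61.3 % / 53.6 % | 1.014 | 0.935 | 0.860 |
| 145 | 5 | 72.4 % / 65.0 % | 1.015 | 0.940 | 0.865 |
| 145 | 8 | 73.2 % / 66.3 % | 1.033 | 0.963 | 0.894 |

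The formula agrees with the first row: 0.984 − 3 × 0.072/3 = 0.912 (simulated 0.913). For d = 5 it gives, at the extremes, 0.970 − 5 × 0.070/3 = 0.853 and 1.033 − 5 × 0.069/3 = 0.918. The loss is thus 4 to 10 % at 3 mmHg, 8 to 15 % at 5 mmHg and 11 to 17 % at 6 mmHg. With no fall the ratio is 0.97 to 1.03, and its direction depends on where the mean lies relative to the threshold. Diastolic ratios are similar: 0.98 to 1.02, 0.92 to 0.96 and 0.86 to 0.90 for falls of 0, 1.5 and 3 mmHg.

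**Baseline adjustment.** A separate simulation fitted the baseline-adjusted comparison with baseline and follow-up under the same rule (true effect −4, mean 130 to 140, between-man SD 13, reading SD 5 to 7). Adjusted estimates were −3.91 to −4.03 with no excess, −3.60 to −3.78 with 3 mmHg and −3.37 to −3.60 with 5 mmHg. These are almost identical to the unadjusted ones.

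**Precision of the alternatives.** In the cell with mean 130, within-visit SD 5 and d = 3, the standardised effects are:
- rule: 0.913 × 3/13.546 = 0.202
- first reading in all: 3/14.855 = 0.202
- mean of readings 2 and 3 in all: 3/14.432 = 0.208

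Uniform readings remove the bias and beat the rule here. The same division favours them in every cell of the table.

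**The case against.** Two stronger conclusions are tempting, and the document supports neither. A reader might infer that the arms are measured differently. They are not: the rule makes no reference to allocation, and re-measurement rates diverge only if the programme has already moved blood pressure. With no effect, the analysed value has the same distribution in both arms, so there is no bias and no false positive. A reader might also infer that the effect is certainly attenuated. Material attenuation requires readings to fall within a visit; no figure is given, and the five minutes of sitting may reduce any fall. Both limits stand.

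It is also fair to say that analysing the first reading in everyone is not free. With a true effect of −4, between-man SD 13, reading SD 7, visit-to-visit SD 8, mean 130 to 140 and an excess of 0, 3 or 5 mmHg, the baseline-adjusted residual SD was 12.3 for the first reading against 10.3 to 11.3 for the rule. Standardised effects were 0.324 to 0.330 against 0.334 to 0.357. This stands, and it makes the first reading the fallback. It does not count against uniform repeat readings.

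The section describes measurement and does not expressly say which value enters the model, and nothing says the first reading is deleted, so a first-reading analysis stays available. That is true. But no other analysed value is defined, and the readings missing below the threshold cannot be recovered. Finally, baseline pressure is recorded before allocation, so the threshold in the covariate alone costs precision and does not bias the comparison.

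**Conclusion.** The point holds in a limited form. The stated rule defines systolic and diastolic pressure differently according to their own level. Under assumed falls of 3 to 5 mmHg within a visit, a true effect would be understated by roughly 5 to 15 %, which is about 0.2 to 0.6 mmHg on an assumed 4 mmHg (4 × 0.05 and 4 × 0.15). With no fall, the bias is within about 3 % in either direction. The size rests wholly on assumed inputs; the level-dependence itself is in the text. The rule also shrinks the SD, so power changes little, and the harm is to the mmHg estimate and its interpretation. Severity is minor to moderate: the activPAL primary outcomes and the sample size are unaffected.

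**What to change.** At every visit, take the same number of readings in every man and define the analysed value from the same ones, for example the mean of the second and third. A constant fall between readings then cancels between arms. The cost is a few extra minutes per man per visit, with the same device and staff. The duty-of-care letters stay as they are.

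If that is not feasible, keep the present procedure and add an analysis of the first reading in all men as a sensitivity analysis. This needs one line in the outcome definition and no new data, and it accepts greater measurement noise.
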